
### 2.7. Data Analysis

After the questionnaires are collected and screened, two researchers will use the EpiData 3.1 database to double-enter the data and will then use SPSS19.0 for statistical analysis (SPSS Inc., Chicago, IL, USA). For the KAP questionnaire, we use frequency to analyze the demographic characteristics of the participants and the mean/median will be used to describe the overall score of each part. We set three options for the knowledge section: yes or no or do not know. If participants answer a question correctly, they get one point, however, if they answer incorrectly or do not know, they get 0 points. For the attitude and behavior section, we will utilize the Likert scale for the statistical analysis. Chi-square test will be applied to compare the knowledge, attitudes, and behavior differences of the guardians about antibiotics in different regions and to evaluate the knowledge, attitudes, and practice differences of the caregivers about antibiotics use for children among people with different demographic characteristics. For the knowledge retention questionnaire, in each section, we will calculate the percentage of each question that is answered correctly. Logistic regression and Pearson correlation coefficient will be used to determine the important factors affecting children’s knowledge of antibiotics, such as regions and school scale and so on.

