### 2.2. Sample Size

Based on the previous study [40], the rate of irrational use of drugs by guardians for their children is 40% to 70%. Through our educational intervention, we hypothesized a 15% reduction in the rate of irrational drug use among children. We set α = 0.05, 1 − β = 0.9. We used software, Sample Size 2.0, to calculate the sample size, and 231 participants are required for the intervention and control groups. Taking into account the lost population, the invalid questionnaires, and the low response rate, we increased the sample size by 55%, to a total sample size of 720. We will select 180 school-aged students in every school. For each child included in our study, we will also invite their caregiver to participate in the study. In four primary schools, we chose 720 students and 720 caregivers. The sampling process is shown in Figure 1. We also invited teachers to help us to do our study. They are the bridge of communication between researchers and caregivers. Caregivers may not follow the orders from researchers, however most parents will follow tasks that are assigned by the teacher and, therefore, we will invite teachers to help us to implement a smooth intervention. In addition, they will help the researchers to distribute and collect the questionnaires from the children and caregivers. Before the intervention, we will give training to the teachers so that they will know more about our study and will clearly know their duty. In each class, we will invite 1 head teacher to cooperate with us.

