### 2.5. Outcome Indicators

For the caregivers, the primary outcome is the proportion of the caregivers who use antibiotics irrationally for their children. If one of the following situations exists, we will define it as irrational drug use: Guardians use antibiotics to prevent colds in children, increase or decrease the dosage of children on their own, reserve antibiotics at home or use residual antibiotics for children. The secondary outcome is scores of caregivers on knowledge, attitude, and behavior of antibiotic use for children. For the school-aged children, the primary outcome is the percentage of each of the questions that are contained in the questionnaires that are answered correctly. The secondary outcome is the scores of each section in the knowledge retention questionnaire.

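### Section 2.7 names an order-blind chi-square test for caregiver Likert and score data in the region and demographic comparisons; an ordinal or mean-based method would fit better (minor)

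*Protocol article*

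**What the plan says.** Section 2.5 of the protocol article defines the caregiver secondary outcome as a set of scores: "The secondary outcome is scores of caregivers on knowledge, attitude, and behavior of antibiotic use for children".

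Section 2.7 explains how the parts are built and summarised:

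- Knowledge items are scored 0 or 1: "If participants answer a question correctly, they get one point, however, if they answer incorrectly or do not know, they get 0 points".
- For the other two parts: "For the attitude and behavior section, we will utilize the Likert scale for the statistical analysis".
- For description, "the mean/median will be used to describe the overall score of each part".

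It then names one test for these quantities: "Chi-square test will be applied to compare the knowledge, attitudes, and behavior differences of the guardians about antibiotics in different regions". The same sentence extends the test to a second use: "to evaluate the knowledge, attitudes, and practice differences of the caregivers about antibiotics use for children among people with different demographic characteristics".

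The section gives no number of Likert levels and no cut-point that would turn a score into categories. It names no mean-based, rank or ordinal test for the caregiver data. It also names no test for intervention against control.

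**The concern.** A Likert response is ordered, and a section score is ordered and numeric. The natural question about a region or a demographic group is whether its level of knowledge, attitude or behaviour is higher or lower. The stated mean or median answers that question.

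The Pearson chi-square test answers a different one: whether the whole distribution over categories is the same. This has two consequences.

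1. The test spreads its sensitivity over k − 1 degrees of freedom, where k is the number of categories. A plain shift in level is detected less often than by a test that uses the order.
2. A small p-value can come from a difference in spread alone. Printed beside two nearly equal means, it would invite the reader to infer a difference in level that is not there.

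At stake is the article's additional aim, in the Introduction, of describing caregivers' knowledge, attitudes and practice patterns. Differences between cities or demographic groups could be missed or misdescribed.

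**Working it through.** **The plan's own figure.** Section 2.2 gives "We set α = 0.05, 1 − β = 0.9" and "we hypothesized a 15% reduction in the rate of irrational drug use among children", with a starting rate of 40% to 70%. At the midpoint of 55%, falling to 40%, two-sided and without continuity correction:

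n = [1.960·√(2·0.475·0.525) + 1.282·√(0.55·0.45 + 0.40·0.60)]² / 0.15² = (1.384 + 0.895)² / 0.0225 ≈ 231 per group.

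Then 2 × 231 × 1.55 = 716, close to the stated 720. The figure reproduces. It belongs to the primary proportion, and this point does not touch it. The article states no power for the scores.

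**Group size for the comparison in question.** There are 180 caregivers per school and two schools per city, so 2 × 180 = 360 per city. Demographic group sizes are not given.

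**Power against a shift in level.** Assumptions: a latent normal score cut into k categories of equal probability in one group and shifted in the other; independent caregivers; two-sided 5%. The shift is set so that the comparison of means has 90% power. The chi-square noncentrality is

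λ = n·Σ(p − m)²/m + n·Σ(q − m)²/m, with m = (p + q)/2,

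and its power is P(noncentral χ² with k − 1 df and noncentrality λ > 5% critical value).

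| k | shift (SD) | λ | df | critical value | chi-square power | mean test |
|---|---|---|---|---|---|---|
| 3 | 0.271 | 10.4 | 2 | 5.99 | 83% | 90% |
| 5 | 0.256 | 10.5 | 4 | 9.49 | 74% | 90% |
| 11 | 0.249 | 10.6 | 10 | 18.31 | 57% | 90% |
| 21 | 0.248 | 10.7 | 20 | 31.41 | 43% | 90% |

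λ hardly changes and stays near (1.960 + 1.282)² ≈ 10.5. The loss comes from the extra degrees of freedom. With k = 2 the chi-square power is also 90%, so single 0/1 items lose nothing.

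Simulation (4,000 runs, 360 per group) agrees:

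- Five levels: chi-square 74%, t-test 90%, Mann-Whitney 90%.
- Sum of ten 0/1 items: chi-square 57%, t-test 90%, Mann-Whitney 89%.

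At 231 per group, with the shift rescaled to keep 90% for the mean test, chi-square has 83%, 73% and 57% for 3, 5 and 11 levels.

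**Equal means, different spread.** Take five levels with (10, 20, 40, 20, 10)% against (15, 20, 30, 20, 15)%. Both means are 3; the variances are 1.2 and 1.6. At n = 360:

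λ = 2·360·(2·0.025²/0.125 + 0.05²/0.35) = 720·(0.0100 + 0.00714) = 12.3.

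On 4 df the chi-square test rejects in 81% of samples (60% at n = 231). The mean test rejects in 5%.

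**Identical distributions.** Simulated chi-square rejection is 4.4% to 5.1%, so the test keeps its nominal level.

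**The case against.** **Chi-square may be meant item by item.** The text does not say outright that summed scores will be cross-tabulated. For 0/1 knowledge items chi-square is suitable, and several behaviour questions in section 2.6 are framed as whether something was done. This stands for knowledge items and any yes/no behaviour item. It does not clear the rest, because section 2.7 puts the attitude and behaviour parts on a Likert scale. Nor would dichotomising restore the power: where a mean test has 90%, a median split gives about 73% and a split at the upper quintile about 65%. No cut-point is stated in any case.

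**It is not the trial comparison.** This stands. A reader might infer that the secondary outcome will be tested between arms by chi-square. The article does not say so: it names the test only for regions and demographic characteristics.

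**Chi-square is a valid test.** This stands too. A reader might take rejection at equal means for an inflated type I error. It is not. The distributions in that example really do differ, and under identical distributions the level holds. The fault is that the p-value and the reported mean address different questions.

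**The size rests on assumptions.** The number of levels and the spreads are not in the article. A table of every value of a long summed score would make the loss look very large, but the article proposes no such table.

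**Conclusion.** The point holds in limited form and is minor. Section 2.7 pairs ordered caregiver data with a test that ignores order. This is a stated choice of method, not detail left to a fuller plan.

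For the city comparison, the cost is a fall from 90% power to roughly 83% (3 levels), 74% (5) or 57% (11), with a risk that a difference in spread is read as one in level. These figures assume the stated numbers of levels, 360 complete caregivers per city and independent responses. Clustering by school is ignored, so they show the relative loss and not the power this trial would achieve.

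The conclusion is confined to the region and demographic comparisons. The primary caregiver outcome is a proportion, for which chi-square suits the data type, and it is unaffected.

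**What to change.** Amend section 2.7 in one or two sentences:

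- Keep chi-square for nominal and yes/no items, including single 0/1 knowledge items.
- Compare section scores by a difference in means with a confidence interval, from a regression of the score on region and demographic factors. Where scores are skewed, use a rank-based or ordinal model.
- Use an ordinal or trend test for single Likert items.
- State the number of Likert levels, so that the reader can see which rule applies to which item.

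The test would then match the reported mean or median. The cost is a short text change: no new data are needed and the sample size calculation is untouched. How to allow for clustering by school is a separate matter that applies to whichever model is chosen.

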## 2. Materials and Methods

### 2.1. Study Design

We will conduct a multistage cluster randomized controlled trial at the school-level. Our study will be carried out in primary schools in the Shaanxi Province, western China. According to the economic level of the Shaanxi Province, two clusters were formed: developed areas, where we chose Baoji, and Weinan from the less developed areas. The chosen primary schools from both of the study sites met the following inclusion criteria: (1) Schools must be willing to take part in our study; (2) Schools should be in urban areas with enough teachers and students. In rural areas, most young people need to go out to work and earn a living, leaving the elderly to look after the children. Socio-demographic characteristics are quite different between rural and urban areas, so we only include urban primary schools. (3) Schools are theoretically matched and are comparable with each other in terms of school size and teaching level; (4) Must be public primary schools because private primary schools are mainly composed of students with higher family incomes. (5) Two schools in each city must be in different districts or in different streets. The distance between the two schools in each city must be more than 5 km. Based on the inclusion criteria and the referenced CONSORT (Consolidated Standards of Reporting Trials) statement for randomized trials [39], a final selection of two primary schools in each city will be made. In total, there are 804 public primary schools in Baoji and 638 public primary schools in Weinan. Among these schools, in Baoji there are 37 schools in urban areas and 767 in county or in rural areas. For the schools in urban areas, 10 schools are unwilling to participate in our study and 17 schools are small scale (which have less than three classes in the fifth grade or less than 1500 students in schools). Taking the distance between the two schools in the same city into account, we chose two schools from the remaining 10 schools. In Weinan, there are 23 schools in urban areas and 615 in counties or in rural areas. The sampling process was similar in Weinan and we have depicted it in Figure 1 (The sampling process). In each city, one primary school will be randomly selected for the intervention group and the other will serve as the control group. The study participants will be chosen from the class level and in every school we will select three to five classes from the fifth grade at random. Participants will be selected based on the inclusion criteria from the chosen classes and they will be blinded on their assigned group.

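### Schools are randomised, but every test named in section 2.7 works at the level of the individual, so tests of between-school contrasts (region, school scale, and the arms if treated the same way) are anti-conservative

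*Protocol article*

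**What the plan says.** Section 2.1 sets the design: "We will conduct a multistage cluster randomized controlled trial at the school-level". Allocation is within city: "In each city, one primary school will be randomly selected for the intervention group and the other will serve as the control group". Classes form a second level: "in every school we will select three to five classes from the fifth grade at random". Section 2.2 fixes the cluster size, "We will select 180 school-aged students in every school", and the total, "In four primary schools, we chose 720 students and 720 caregivers".

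Section 2.7 names three inferential methods. The first is for caregivers: "Chi-square test will be applied to compare the knowledge, attitudes, and behavior differences of the guardians about antibiotics in different regions". The same sentence goes on to comparisons between demographic groups. The other two are for children: "Logistic regression and Pearson correlation coefficient will be used to determine the important factors affecting" children's knowledge of antibiotics, with region and school scale given as examples of such factors.

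The end of section 2.1 promises a comparison of pre- and post-intervention data between the arms, and section 3 says that this will give the net effect of the intervention. Section 2.7 names no test for it. Nowhere does the article mention an ICC, a design effect, random effects, generalised estimating equations, robust variance or school-level summaries.

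**The concern.** Chi-square, ordinary logistic regression and Pearson correlation treat each child or caregiver as an independent observation. Pupils of one school share teachers, neighbourhood and class, and their families share local habits, so their answers are likely to be correlated. A factor that takes one value per school is then informed by four schools, not by 720 people. With clusters of 180, even a small correlation makes the nominal standard error clearly too small.

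At stake is how the results are used. Sections 3 and 4 make extension to more schools, and advice to policy-makers, depend on positive results. An ordinary difference between two pairs of schools could then pass as a regional difference or, if the arms were tested in the same way, as an intervention effect. Section 3 does concede that few schools are included, but treats this only as a limit on generalisation, not on inference.

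**Working it through.** **Inputs.** From section 2.1: 2 cities, 4 schools, 2 per arm, 3 to 5 classes per school. From section 2.2: m = 180 per school (360 per arm), "We set α = 0.05, 1 − β = 0.9", an expected rate of irrational use of 40% to 70%, a hypothesised reduction of 15%, and 231 required participants. Assumed: an ICC of 0.005 to 0.05, because none is given.

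**1. The plan's own figure.** Take the midpoint rate of 55%, an absolute reduction to 40%, a two-sided test and pooled variance:

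n per arm = [1.960 × √(2 × 0.475 × 0.525) + 1.282 × √(0.55 × 0.45 + 0.40 × 0.60)]² / 0.15² = [1.384 + 0.895]² / 0.0225 ≈ 231.

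The stated figure is reproduced (0.60 against 0.45 also gives 231). Then 231 × 1.55 = 358 per arm, about 716 in all, rounded to 720. This is a calculation for independent individuals (design effect 1). The 55% is attributed to losses, invalid questionnaires and low response, none of it to clustering. The sample size thus makes the same independence assumption as the analysis.

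**2. A contrast of two schools with two schools.** This is the structure of the region comparison (reading regions as the two cities) and of the arm comparison.

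Design effect: DEFF = 1 + (m − 1) × ICC. Real type I error of a nominal 5% test: 2 × [1 − Φ(1.96 / √DEFF)]. Example at ICC 0.01: DEFF = 1 + 179 × 0.01 = 2.79, √DEFF = 1.67, 1.96 / 1.67 = 1.17, error 0.241.

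| Assumed ICC | DEFF | SE too small by factor | Real type I error | Simulated |
|---|---|---|---|---|
| 0.005 | 1.90 | 1.38 | 0.155 | 0.153 |
| 0.01 | 2.79 | 1.67 | 0.241 | 0.238 |
| 0.02 | 4.58 | 2.14 | 0.360 | 0.367 |
| 0.05 | 9.95 | 3.15 | 0.534 | 0.538 |

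The last column is a beta-binomial simulation (four schools, 20,000 runs). With about 116 analysable per school (231 / 2), the errors are 0.118 / 0.181 / 0.281 / 0.451.

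These figures are for an unadjusted comparison at a single time. For region they describe the baseline, when the arms do not yet differ.

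**3. School scale.** This factor has at most four distinct values, one per school. A correlation over 720 children treats at most four points as 720.

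**4. What four schools can support, whatever the ICC.** Allocations: 2 × 2 = 4. Mirror images give the same absolute statistic, so the smallest two-sided randomisation p is 2/4 = 0.5 (one-sided 0.25). A school-level t-test has 4 − 2 = 2 degrees of freedom (critical value 4.30), or 2 − 1 = 1 if paired by city (critical value 12.7).

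**The case against.** The strongest objection is that none of the named tests is assigned to the arms. A reader might infer that the chi-square is the test of the intervention effect, or that a false intervention effect will be reported. The text supports neither. The chi-square is for regions and demographic groups, and the regression and correlation are for factors behind children's knowledge. The missing arm test alone would not be a finding either, because a condensed article may leave it to a fuller document.

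Three further points count. First, it would be wrong to say that section 2.7 ignores the city stratum: region appears there, as a factor of interest, though not as a stratum for the arm effect. Second, demographic factors vary within schools, and for them the inflation can be slight. Third, schools are matched on size and teaching level, randomised within city and measured before and after. The correlation that matters for a within-city change may therefore be smaller than a raw ICC, and the type I errors above may overstate the problem for that analysis.

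All of this narrows the point but does not remove it. Region and school scale are named in section 2.7 and vary only between schools. The article commits to specific methods for them that do not fit its design, and nothing in it protects the promised arm comparison from the same treatment. Logistic regression could in principle carry random effects or robust variance, but the article mentions neither.

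**Conclusion.** Wrong as written, within limits. The individual-level methods of section 2.7 do not suit the planned tests of region and school scale, and would not suit the arm comparison. At 180 per school, a nominal 5% test of such a contrast has a real error of about 15% at an assumed ICC of 0.005, rising to about 53% at 0.05. The size rests on that assumed range and on an unadjusted, single-time comparison. The direction needs only a positive within-school correlation.

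The statement that four allocations and 1 to 2 degrees of freedom cannot carry a confirmatory arm claim needs no ICC. A reader might also infer that a mixed model would repair this. It would not: with city and arm as fixed effects, four schools leave one degree of freedom, and the school variance could barely be estimated.

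**What to change.** Amend section 2.7 as follows.

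- Make the primary arm estimate the within-city difference (intervention minus control school) in change from baseline, averaged over the two cities.
- Show its standard error multiplied by √DEFF over a stated ICC range, for example 0.005 to 0.05 (factors 1.38 to 3.15 at 180 per school).
- Optionally add a mixed model with random effects for school and class, city as a fixed stratum and small-sample degrees of freedom, noting that it cannot create degrees of freedom.
- Report region and school-scale comparisons descriptively, or with school as the unit.
- State that the arm comparison is exploratory and that no significance claim rests on tests that ignore school.

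The cost is a change of wording and modest extra analysis, with no new data. The downside is wider intervals, where intervals are reported, and a weaker claim.

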## Abstract

(1) Background: Antibiotic resistance is an imperative public health issue globally. Major factors that are resulting in this trend are the irrational and excessive use of antibiotics. Children account for a greater population of antibiotics use, therefore, an educational intervention on the rational use of antibiotics for children and caregivers will be beneficial. (2) Methods: A randomized controlled and parallel group study of fifth grade children and their caregivers will be evaluated in four primary schools in Baoji and Weinan of the Shaanxi Province. Two primary schools will be randomly selected for the educational intervention and two schools will serve as a control group. In the intervention arm, educational interventions will be conducted among caregivers and their children. The intervention measures include interactive training sessions, booklets, and printed or electronic educational materials that will be given to the caregivers or the school-aged children. In the control arm, no interventions will be implemented. Baseline data collected from June, 2018 and the intervention will last for three months. Knowledge-Attitude-Practice (KAP) questionnaires will be used to evaluate the caregivers’ knowledge, their attitude, and their practice. Knowledge-Retention questionnaires will be used to assess the children’s knowledge about microbes, antibiotics, and hygiene. (3) Discussion: This study is a unique comprehensive intervention targeting both children and their caregivers. We hypothesize a decrease in the irrational use of antibiotics among the studied population. Hence, this result would provide evidence for policy makers and educational departments for the implementation of similar interventions on the rational use of antibiotics.

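### Region and school scale are to be tested on individuals, but four schools chosen to be similar in size cannot separate either factor from differences between particular schools

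*Protocol article*

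**What the plan says.** Section 2.1 sets the level of the design: "We will conduct a multistage cluster randomized controlled trial at the school-level". The Abstract gives four schools: "Two primary schools will be randomly selected for the educational intervention and two schools will serve as a control group". Region has two values, each represented by one city, since Section 2.1 says "two clusters were formed: developed areas, where we chose Baoji, and Weinan from the less developed areas". Allocation is within city: "In each city, one primary school will be randomly selected for the intervention group and the other will serve as the control group".

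School size is restricted in two ways in the same section. One inclusion criterion reads "Schools are theoretically matched and are comparable with each other in terms of school size and teaching level". In Baoji, small-scale schools are also removed before selection, small being defined as those "which have less than three classes in the fifth grade or less than 1500 students in schools". The Weinan process is described as similar.

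Section 2.2 takes 180 children per school, 720 in total, with one caregiver for each child.

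Section 2.7 then plans logistic regression and Pearson correlation to identify factors affecting children's "knowledge of antibiotics, such as regions and school scale and so on". It also plans a chi-square comparison of caregivers' knowledge, attitudes and behaviour between regions. It mentions no school term and no allowance for clustering in these analyses.

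**The concern.** Region and school scale are properties of a school. All children in one school share the same value, so more children per school make that school's own result more precise but add nothing on how schools differ within a region or at a given size. Each city contributes two schools. If the two Baoji schools score differently from the two Weinan schools, the data cannot show whether this reflects economic level or the particular schools chosen.

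Scale is weaker still. It takes at most four values, and the selection rules in Section 2.1 were written to keep those values close together. Section 2.7 therefore tests a factor whose range Section 2.1 deliberately narrows.

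At stake is the additional aim in the Introduction, to describe knowledge and practice patterns, together with the intention in the Conclusions to pass findings to the education sector and policy-makers. An ordinary difference between particular schools could be published as an effect of region or school size, with a p-value computed as if several hundred independent observations supported it.

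**Working it through.** **The plan's own figure.** The protocol gives no figure for the region or scale analyses. Its only sample size is for the caregiver primary outcome. With 55% versus 40% (the midpoint of the 40% to 70% range, less 15 points), two-sided α 0.05, power 0.90 and pooled variance:

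n = [1.960·√(2 × 0.475 × 0.525) + 1.282·√(0.55 × 0.45 + 0.40 × 0.60)]² / 0.15² = 230.8, so 231 per group.

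2 × 231 × 1.55 = 716, close to the stated 720. The figures reproduce as a calculation for independent individuals. Without the inflation, 462 / 4 ≈ 116 per school, used below as the evaluable number if all the planned allowance is lost.

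**Inputs.** Four schools, two per city (Abstract, Section 2.1); 180 per school (Section 2.2), or 116 as above; nominal two-sided 5% test. The ICC is not in the document, so a range of 0 to 0.05 is assumed.

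**School-level information on region.** Four schools less two parameters (intercept and region) leave 2 degrees of freedom.

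**Type I error of an individual-level test of region.** Design effect DE = 1 + (m − 1) × ICC. True type I error = 2 × [1 − Φ(1.96 / √DE)].

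| ICC | DE, m = 180 | Type I error | DE, m = 116 | Type I error |
|---|---|---|---|---|
| 0 | 1.00 | 5% | 1.00 | 5% |
| 0.01 | 2.79 | 24% | 2.15 | 18% |
| 0.02 | 4.58 | 36% | 3.30 | 28% |
| 0.05 | 9.95 | 53% | 6.75 | 45% |

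For example, at ICC 0.01 and m = 180, 1.96 / √2.79 = 1.173, which gives 0.24. A simulation of the simple two-city comparison (four schools of 180, 50% correct, no true effects) agreed: 5%, 24%, 36% and 54% at ICC 0, 0.01, 0.02 and 0.05.

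**The same point as a difference between cities.** Take 50% correct and 360 children per city. The individual-level test declares significance at 1.96 × √(2 × 0.25 / 360) = 7.3 percentage points. A school-level test on 2 degrees of freedom has critical t = 4.30 and would need about 4.30 × √(2 × 0.25 × DE / 360). That is 27, 34 or 51 points at ICC 0.01, 0.02 or 0.05.

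**Relation to arm.** Each city has one school in each arm. Coding city and arm as ±1, the products over the four schools are +1, −1, +1, −1 and sum to 0, so region and arm are uncorrelated by design. Scale has no such protection. If the two schools in a city differ in size, the larger one is wholly in one arm, so within that pair size and arm move together. This matters only in post-intervention data, because at baseline there is no intervention effect.

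**The case against.** The strongest reply is that this is a descriptive side aim, that the article already admits in its Discussion that few schools are included and that results cannot be generalised, and that a fuller analysis plan may add a clustering adjustment. The first part stands and limits the weight of the point. The second does not meet it: the Discussion does not say that region and scale are indistinguishable from school, and Section 2.7 keeps the tests. Nor does the third, since an adjustment can correct a standard error but cannot supply more than four schools or restore the size variation that selection narrowed.

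The type I error figures also depend on an ICC that the protocol does not give. That is correct. They show a risk that grows with the ICC and vanishes at zero.

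A reader might infer more than the text supports:

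- **That region is mixed with the intervention effect.** It is not, because randomisation is within city.
- **That the regressions will produce spurious findings.** The supportable statement is a raised false-positive risk.
- **That no degrees of freedom remain.** This would follow if arm, region and scale all entered one model with an intercept, four parameters for four schools. Section 2.7 does not specify that model.
- **That the design removes all size variation.** Section 2.1 sets a floor and asks for comparability, and three to five classes are drawn per school. Variation is narrowed, not abolished.
- **That the methods are the wrong type.** A Pearson coefficient with a two-category variable is a valid point-biserial correlation. Logistic regression fits an item scored correct or incorrect, which is the children's primary outcome in Section 2.5.

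**Conclusion.** The point holds in a limited form. With two schools per city, selected to be comparable in size, effects of region and school scale cannot be distinguished from differences between particular schools. The individual-level tests in Section 2.7 overstate significance whenever the ICC is above zero. For region the true type I error is about 24% to 53% at an assumed ICC of 0.01 to 0.05 with 180 per school, or about 18% to 45% with 116. These figures rest on the assumed ICC, equal school sizes and no clustering adjustment in the analysis. The lack of school-level replication does not depend on the ICC value.

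Confounding with arm is possible only for scale, within a city pair and after the intervention. The point concerns a secondary aim and does not change any conclusion about the intervention effect.

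**What to change.** In Section 2.7:

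1. Drop school scale as a tested factor.
2. Keep city as the randomisation stratum, and report city differences descriptively, school by school, without p-values. This applies to the caregiver chi-square comparison by region as well as to the children's analysis.
3. Limit the factor analysis to individual characteristics already collected, such as caregiver education, family income and relationship to the child, with a term for school in the model, and label it exploratory. Using baseline data only is one simple way to keep the intervention effect out of it.

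The cost is one or two sentences and no new data. The real downside is that the trial gives up its claims about region and school size, which four schools cannot support.
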